### Intervention/Comparison

Watchful waiting: no immediate provision of antibiotic therapy at the time of enrolment. Subsequent treatment, including antibiotic prescription, is at the discretion of the treating physicianAntibiotic group: immediate prescription of antibiotic therapy (choice of antibiotic recommended to be based on Australian prescribing guidelines [36])

### Relevant concomitant care and interventions

Any concomitant care or intervention is permissible at the discretion of the treating physician and parent/carer. We will record analgesia and other symptom relief and concomitant care.

### Eligibility criteria

#### Inclusion

Aboriginal and/or Torres Strait Islander child (as documented by the health service)Aged 2 years to 16 years (inclusive)Not previously enrolled in the studyCurrent AOM without perforation diagnosed by the treating physician based on a Type B tympanogram and at least one of the following:bulging of the eardrum on otoscopy,ear pain (or irritability in 2 to 3 year-olds)

#### Exclusion

The child has been taking any antibiotic in the previous 4 daysAt high risk of CSOM, as defined by residing in a geographic area known to have prevalence of CSOM greater than 4 %A grommet in situ, or a current or past history of tympanic membrane perforationA condition which increases the risk of complications (including immunosuppression, genetic or chromosomal abnormality, cleft palate or mid-face abnormalities such as seen in Down syndrome)Systemic features necessitating antibiotic treatment (including septicaemia, meningitis, pneumonia, or urinary tract infection)

### Primary outcome

Proportion of children with clinical resolution of AOM, defined as all of the following: no pain, fever not higher than 38 °C, no bulging eardrum and no complications of OM (no perforation or mastoiditis) assessed by:GP or nurse practitioner clinical examination on day 7 (acceptable range days 5 − 10)Where 1. is not available, GP or nurse practitioner assessment of parental report and review of VO (recorded by trained RO), and no fever of at least 38 °C

### Secondary outcomes

Proportion of children with resolution of signs of AOM, through blinded otolaryngologist assessment of VO images and tympanometry taken at days 0 and 7* by a trained ROProportion of children with middle ear effusion, perforation and CSOM at week 7*, assessed by an independent blinded observer (otolaryngologist) reviewing VO and tympanometry dataProportion of children with new antibiotic prescriptions (where ‘new’ is any antibiotic prescription provided after the recruitment consultation) for an index case of AOM assessed by review of medical record and by parent/carer reportParent/carer-reported time to resolution of AOM symptoms assessed by parent/carer symptom report at days 3*, 7* and 14*, including the AOM Faces Scale [37]Usage of analgesia for AOM symptom relief assessed by parent/carer reportParent/carer satisfaction with AOM treatment assessed by parent/carer report using rating scale

(*acceptable ranges: days 2 − 4; days 5 − 10; days 11 − 17; weeks 6 − 8)

### Processes of enrolment and subsequent assessments

The enrolment processes are shown in Fig 1. Children will undergo subsequent assessments via phone or face-to-face at days 3, 7, and 14 and week 7. Medically-trained chief investigators will review participant medical records for any additional information relating to ear disease and/or its treatment which occurred in the 3 months following recruitment. Details of data collection at each of the scheduled assessment times are summarised in Table 1.

**Fig. 1 Fig1:**
[figure not shown]
Participant enrolment flowchart

**Table 1 Tab1:** Schedule of assessments – child/parent/carer

Assessment		Screening/Randomisation	Post-randomisation^a^				
	Performed by	Day 0	Day 3	Day 7	Day 14	Week 7	3 months
			(Days 2 − 4)	(Days 5 − 10)	(Days 11 − -17)	(Weeks 6 − 8)	(no window)
Clinical assessment	GP/NP	X		X			
Temperature	GP/NP/Health service RO or AI	X		X			
Tympanometry	GP/NP/AMS Health service RO or/AMS AI	X		X		X	
Digital video-otoscopy	GP/NP/Health service RO or AI	X		X		X	
Health history and socio-demographics	Health service RO/AI	X					
Symptoms questionnaire	AMS Health service RO/AMS AI	X	X	X	X		
Progress questions	AMS Health service RO/AMS AI		X	X	X	X	
Serious adverse events/severe study- related adverse events	AMS Health service RO/AMS AI		X	X	X	X	
Review Parent/Carer/Child Diary -symptom assessment using AOM-Faces Scale	AMS Health service RO/AMS AI		X	X	X		
Medical record review	Medical record reviewer						X

*AI* associate investigator, *AMS* Aboriginal Medical Service, *GP* general practitioner, *NP* nurse practitioner, *RO* research officer

^a^Bracketed day/week numbers in the Post-randomisation column above represent acceptable time ranges.

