**Methods/Design:**

This non-inferiority multi-centre randomised controlled trial will determine whether watchful waiting is non-inferior to immediate antibiotics for urban Aboriginal and Torres Strait Islander children with AOM without perforation. Children aged 2 − 16 years with AOM who are considered at low risk for complications will be recruited from six participating urban primary health care services across Australia. We will obtain informed consent from each participant or their guardian. The primary outcome is clinical resolution on day 7 (no pain, no fever of at least 38 °C, no bulging eardrum and no complications of AOM such as perforation or mastoiditis) as assessed by general practitioners or nurse practitioners. Participants and outcome assessors will not be blinded to treatment. With a sample size of 198 children in each arm, we have 80 % power to detect a non-inferiority margin of up to 10 % at a significance level of 5 %, assuming clinical improvement of at least 80 % in both groups. Allowing for a 20 % dropout rate, we aim to recruit 495 children.

We will analyse both by intention-to-treat and per protocol. We will assess the cost- effectiveness of watchful waiting compared to immediate antibiotic prescription. We will also report on the implementation of the trial from the perspectives of parents/carers, health professionals and researchers.

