**Discussion:**

The trial will provide evidence for the safety and effectiveness of watchful waiting for the management of AOM in Aboriginal and Torres Strait Islander children living in urban settings who are considered to be at low risk of complications.

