### Design

We are using a non-inferiority, open-label, randomised controlled trial (RCT) design. Non-inferiority studies seek to determine if a new treatment is no worse than a reference treatment by a predetermined margin. The new treatment is recommended if it is similar or better than the previous treatment, usually on the premise that the new treatment has other advantages over the reference treatment [31]. Children will be randomised to watchful waiting or immediate antibiotic therapy, stratified by study site and age of child (2 − 6 years and 7 − 16 years), using the National Health and Medical Research (NHMRC) Clinical Trial Centre Interactive Voice Response System (IVRS). It is not possible to blind the patient or treating staff. Outcome measurements will be verified by blinded assessment of tympanometry and video-pneumatic otoscopy (VO) data by an otolaryngologist and analysis will be blinded.

For practical reasons, the participating sites will commence staggered recruitment, commencing in two sites per block, 6 months apart. We will undertake cost-effectiveness analysis and a qualitative study in conjunction with the RCT as an integral part of the study design, with planning for both having commenced at inception [32]. A Data Safety Monitoring Board will oversee the conduct of the trial.

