#### Quality-adjusted Life Years (QALYs)

We will calculate QALYs using CRF data from parent/carers. The CRF data will be used to measure the time a child spends in different health states associated with both the natural course of the disease (mostly characterised by pain), and complications (such as rash or gastrointestinal problems). Each health state will be assigned a utility value (that measures the degree of preference society places on that health state) using QALY weights found in the medical literature, since a novel evaluation of preferences is not in the scope of this trial. QALYs will then be computed by combining the information about the time spent in the different health states with the QALY weights.

Missing cost-effectiveness data will be managed through the use of imputation, rather than deleting observations. Sensitivity analysis is particularly important, since QALY weights currently available are not specific to the Aboriginal and Torres Strait Islander population. Sensitivity analysis will be performed using both one-way and multi-way Monte Carlo simulations, and will allow us to estimate how much the uncertainty regarding QALY estimates contributes to the overall results. In both cases the key output is the set of conditions under which the ICER remains in an acceptable range, in order for watchful waiting to be considered cost-effective.

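### The only adverse-event row in Table 1 records severe non-serious events only when study-related, a condition that can work differently by arm in this open-label trial

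*Protocol article*

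**What the plan says.** Table 1 (Schedule of assessments) contains a single row for adverse events: "Serious adverse events/severe study- related adverse events". It is marked for day 3, day 7, day 14 and week 7, and the column for who performs it reads "AMS Health service RO/AMS AI", that is, the site research officer or associate investigator.

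On blinding, the Design section says "It is not possible to blind the patient or treating staff", and the Abstract adds "Participants and outcome assessors will not be blinded to treatment". Under Intervention/Comparison, the watchful-waiting arm has "no immediate provision of antibiotic therapy at the time of enrolment", with later antibiotics left to the physician; the other arm is prescribed an antibiotic at once.

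On harms, the Abstract says the trial will give "evidence for the safety and effectiveness of watchful waiting". The Secondary objectives list complication rates. The Analysis section plans a secondary per-protocol analysis that will describe early benefit and harm from antibiotics, without naming its data source. Adverse events are not among the Secondary outcomes.

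**The concern.** The row has two parts with different entry rules. A serious event needs no causal link to be recorded. A severe event that is not serious needs one. Relatedness is a judgement made after randomisation, and here it is made in a trial where treatment is known.

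A severe rash or severe vomiting in the antibiotic arm has an obvious candidate cause within the study. The same event in a watchful-waiting child has none, unless an antibiotic was started later. Severe worsening in a child without an antibiotic can be put down to the disease. If judgements run that way, events under antibiotics enter the record more readily than the same events under watchful waiting.

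This matters because the balance of harms is part of the case for watchful waiting: the Background cites more side effects with immediate antibiotics as a reason to withhold them. A count that depends on attribution could overstate antibiotic harm or understate harm from waiting, and both errors favour watchful waiting. An event never entered cannot be recovered at analysis.

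**Working it through.** The article states no adverse-event rate, so there is no figure of the plan to reproduce on this point. The check is a reading of the text, followed by arithmetic on assumed inputs.

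**1. What the row requires.** Serious: no condition on cause. Severe and not serious: must be study-related. This is a stated rule, not an omission.

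**2. Whether the condition can differ by arm.** It can, if the person judging relatedness knows the arm and the arms differ in what can be blamed. Patients, treating staff and outcome assessors are unblinded, and only one arm is prescribed an antibiotic at enrolment. The blinded otolaryngologist reviews video-otoscopy and tympanometry; no blinded step is described for this row.

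**3. What else captures these events.**
- Rash and gastrointestinal problems: the QALY section uses parent/carer case report form data on time spent in health states, including "complications (such as rash or gastrointestinal problems"). No relatedness or severity condition is stated.
- Symptoms and progress: questionnaires in Table 1, with no such condition.
- Ear complications: perforation and mastoiditis within the primary outcome; perforation and CSOM at week 7 by blinded otolaryngologist.
- Medical record review: "any additional information relating to ear disease and/or its treatment which occurred in the 3 months following recruitment". This is limited by topic, so a severe event not linked to the ear or its treatment falls outside it.

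These routes cover much of the ground. None is an unfiltered record, by arm, of severe events of any kind.

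**4. How large the distortion could be.** Let *r* be the true risk of a severe non-serious event, assumed equal in both arms, and *q* the probability that such an event is called study-related.

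Expected number recorded = *n* × *r* × *q*, and recorded ratio (antibiotic / waiting) = *q*(antibiotic) / *q*(waiting).

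*n* = 198 per arm is the evaluable number in Sample size and power (2 × 198 / 0.80 = 495 recruited), used here only as a scale. All values of *r* and *q* are assumptions.

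| *r* | *q*, antibiotic v waiting | Recorded per 198 | Difference (points) | Ratio |
|---|---|---|---|---|
| 5% | 50% v 50% | 5.0 v 5.0 | 0 | 1.0 |
| 4% | 50% v 40% | 4.0 v 3.2 | 0.4 | 1.25 |
| 5% | 60% v 30% | 5.9 v 3.0 | 1.5 | 2.0 |
| 4% | 75% v 25% | 5.9 v 2.0 | 2.0 | 3.0 |
| 2% | 60% v 10% | 2.4 v 0.4 | 1.0 | 6.0 |
| 5% | 60% v 10% | 5.9 v 1.0 | 2.5 | 6.0 |
| 10% | 60% v 10% | 11.9 v 2.0 | 5.0 | 6.0 |
| 5% | 30% v 60% | 3.0 v 5.9 | −1.5 | 0.5 |

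For example, 198 × 0.05 × 0.60 = 5.9 and 198 × 0.05 × 0.10 = 1.0. The ratio does not depend on *r* or *n*. The last row shows the reverse direction, which is possible if harm from withheld antibiotics is counted as study-related.

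If true risks differ, the recorded ratio is the true ratio times the attribution ratio. A true ratio of 0.5 (twice the risk under waiting) with attribution of 60% v 30% gives 0.5 × 2.0 = 1.0, and the difference disappears from the record.

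**The case against.** The strongest reply is that a short row label in a journal article is thin evidence. Definitions of serious, severe and related, and the procedure for judging causality, normally sit in the full protocol, which is not shown. That stands for the definitions, whose absence is no criticism. It does not dispose of the point, because the condition is printed in the row and a definition of study-related would refine it, not remove it.

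Several stronger readings are tempting, and the documents do not support them:

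- *Severe events go unrecorded unless attributed.* Not so. The most obvious examples, rash, vomiting and ear deterioration, are also collected by routes with no stated relatedness condition, some of them read blind. Serious events are unconditional.
- *The trial's safety comparison measures attribution.* No by-arm comparison of this row is specified. The harm objective is complication rates, exemplified by perforation and mastoiditis, and these do not pass through this row.
- *A distorted count goes to the Data Safety Monitoring Board.* The article gives the board an oversight role but does not say what it receives, or whether by arm.
- *Site staff decide relatedness.* This is inferred. The column says who carries out the assessment, not who judges cause.
- *Study-related means caused by the drug.* It need not. In a trial of two strategies it could include harm from withholding antibiotics, and watchful-waiting children may receive antibiotics later.

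It is also fair to say that the arithmetic returns whatever attribution rates are put in. With equal rates the ratio is 1.0.

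**Conclusion.** The point holds in a limited form. Recording of severe non-serious events in the one adverse-event row depends on a causal judgement that can differ by arm, so harm counts drawn from that row could partly reflect attribution.

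The size is not known. In the illustrations the spurious ratio runs from none (1.0) to six-fold. The direction is not certain either, since it turns on what study-related covers. The conclusion rests on two things: the plain reading of the row, and the possibility, not shown by the documents, that attribution differs between arms.

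It does not reach the primary outcome or the blinded ear outcomes. It is worth correcting because the trial claims evidence on safety and plans to describe harm from antibiotics, and the other routes do not replace an unfiltered record of severe events. I would class it as a cheap improvement.

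**What to change.** Reword the Table 1 row to: *Serious adverse events and all severe adverse events, whatever the judged relationship to the study*. Keep the same contacts (day 3, day 7, day 14, week 7) in both arms. Record relatedness as a descriptive field only, not as a condition for entry. Describe harms by randomised arm from these records, together with the unfiltered case report form items on rash and gastrointestinal problems.

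The cost is a wording and form change and slightly more recording by research officers at contacts that already take place. Recruitment has started at five sites, so events recorded under the present row should be marked as such.

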### Data collection and data management

Data collected during each study visit will be recorded using standardised case report forms (CRFs). Data from paper CRFs will be entered into an electronic database by the ROs at each of the participating sites, ideally within 2 weeks of data collection. Electronic CRFs will have participant identifying details removed and be labelled with coded identifiers including randomisation number. Initially, 10 % of paper CRFs will be crossed checked against electronic CRFs for accuracy by a Western Sydney University RO, with a more intensive review conducted as indicated. Data discrepancies will be discussed with and amended by the site accordingly. Randomisation allocation is generated and stored separately from the electronic database and will only be forwarded to the study statistician upon request.

### Sample size and power

With 198 children in each arm of the study, the study will have 80 % power to detect a non-inferiority margin of up to 10 % at a significance level of 5 %, assuming a clinical improvement rate of at least 80 % in both study groups [38]. Allowing for a dropout rate of up to 20 % at days 5 − 10, the total sample size required is 495 children.

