### Analysis

The primary outcome measure is clinical resolution on day 7 as defined above. We will compare the proportion of children meeting the definition of clinical resolution using intention-to-treat analysis (ITT), as well as per-protocol analysis, as non-inferiority trials that use only ITT can be biased towards finding non-inferiority [39]. The per-protocol population will consist of all randomised patients who have adhered to the allocated treatment, were not lost to follow-up, and who have no major protocol deviations. All participants with complete outcome information at day 7 will be included. For protocol deviations where participant data are available, these will be analysed and the impact of their inclusion assessed and reported.

Sensitivity analyses will describe the impact of the following alternative assumptions: (1) missing = clinical failure; (2) missing = clinical success; (3) extrapolation from days 2 − 4 telephone interview; (4) best case for watchful waiting; and (5) worst case for watchful waiting. A secondary per-protocol analysis (accounting for non-adherence and change in treatment) will be done to describe any short-term benefits and harms associated with antibiotic use.

Non-inferiority of watchful waiting compared with antibiotic treatment will be accepted if the lower bound of the 95 % CI around the estimated difference in the primary endpoint rates does not exceed 10 %.

Data analysis will include analysis using Fisher’s exact and Chi-square tests for categorical outcomes, and parametric and non-parametric tests for continuous measures, as required. The difference in the primary endpoint between the two groups will be expressed as a risk difference. Where appropriate, odds ratios (ORs) will be calculated and will include both unadjusted (crude) and adjusted ORs. Adjusted ORs will be obtained using multivariable logistic regression, adjusting for baseline covariates. Time to resolution of AOM symptoms will be modelled using a multilevel Cox (proportional hazards) regression analysis and graphically displayed using Kaplan-Meier curves. Secondary analyses by stratification factors (recruitment site and age) will be carried out, numbers permitting.

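### 198 children per arm give 80% power only at one-sided 5%; under the trial's own 95% CI rule the power is about 70%

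*Protocol article*

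**What the plan says.** The section Sample size and power puts the power of 198 evaluable children per arm at 80%. It words this as "power to detect a non-inferiority margin of up to" a limit, which it sets at 10 percentage points. The error rate appears only as "at a significance level of 5" per cent. The outcome premise is given as "assuming a clinical improvement rate of at least 80 % in both study groups". The section then allows for up to 20% dropout and arrives at 495 children. The abstract repeats the claim with the same figures. Neither place says whether the 5% is one-sided or two-sided.

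The decision rule is in the Analysis section and begins "Non-inferiority of watchful waiting compared with antibiotic treatment will be accepted if the lower bound of the"; the interval it names is the 95% CI for the difference in resolution rates, whose lower limit must stay within 10 points. The difference is to be expressed as a risk difference. The article nowhere mentions a one-sided interval or a 90% CI.

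The Analysis section also plans both an intention-to-treat and a per-protocol comparison. The per-protocol set leaves out children who did not adhere, were lost to follow-up or had major protocol deviations.

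**The concern.** A sample size and the rule it serves must use the same error rate. An unqualified 95% CI around a difference is conventionally two-sided, so using its lower bound to decide is a test at one-sided 2.5%. If the sample size was worked out at one-sided 5%, the trial is judged by a stricter test than the one it was powered for, and the 80% in the abstract and the sample-size section is too high.

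Two things are at stake. The first is the chance that the trial ends without a conclusion although the two strategies are equally good. The second is how a borderline result is read. If the 90% CI cleared the margin and the 95% CI did not, the sample-size section could be cited for one conclusion and the Analysis section for the other.

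**Working it through.** **Inputs from the article.** Resolution p = 0.80 in both arms (the floor of the stated assumption), so the true difference is 0; margin 0.10 as an absolute risk difference; 198 evaluable per arm, 1:1; target power 80%; dropout 20%; decision on the lower bound of the 95% CI. I read the rule as requiring that bound to lie above −0.10.

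**1. Reproducing the stated figure.** With the unpooled normal approximation,

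n per arm = 2p(1−p)(z_α + z_β)² / margin² = 0.32 (z_α + 0.8416)² / 0.01.

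- One-sided 5% (z_α = 1.6449): 32 × 2.4865² = 197.8, so 198. This is the stated number.
- Total with dropout: 2 × 198 / 0.8 = 495. This also matches.

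Other non-inferiority or equivalence readings do not give 198. A continuity correction gives about 218 at one-sided 5% and 271 at one-sided 2.5%, and a two-sided equivalence test gives about 275. A two-sided superiority comparison of 80% with 90% gives 199, but that is a different design and contradicts the assumption of equal rates.

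**2. Sample size under the 95% CI rule.** With z_α = 1.9600: 32 × 2.8016² = 251.2, so 252 per arm. Recruited: 2 × 252 / 0.8 = 630. The plan is 252 − 198 = 54 evaluable children per arm short, or 630 − 495 = 135 recruited.

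**3. Power at 198 per arm.** SE = √(0.32/198) = 0.0402 and 0.10/SE = 2.487.

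| Rule | Power = Φ(2.487 − z_α) |
|---|---|
| 90% CI (one-sided 5%) | Φ(0.843) = 80.0% |
| 95% CI (one-sided 2.5%) | Φ(0.527) = 70.1% |

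Exact binomial enumeration for the 95% CI gives 70.6% with a Wald interval and 70.4% with a Newcombe interval. For the 90% CI it gives 80.0% (Wald) and 80.1% (Newcombe).

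**4. When the stated 80% would hold under the 95% CI rule.**

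- With a larger margin: 2.8016 × 0.0402 = 0.113, i.e. 11.3 points instead of 10.
- With higher resolution in both arms: power at 198 per arm is 79.6% at 85% and 91.3% at 90%, and passes 80% at about 85.2%.
- Less dropout does not quite suffice: with all 495 evaluable (247.5 per arm) and 80% resolution, power is 79.4%.

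**5. Per-protocol set (illustration only).** The 20% allowance is described as dropout and does not separately cover non-adherence or major deviations. The article gives no rate for these, so the further loss from the 198 is my assumption. Power under the 95% CI rule, Φ(0.10/√(0.32/n) − 1.96), is then:

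| Assumed further loss | n per arm | Power |
|---|---|---|
| 5% | 188 | 67.9% |
| 10% | 178 | 65.5% |
| 20% | 158 | 60.3% |

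**The case against.** **Sidedness is not stated.** Only the lower bound matters, and if it were meant as a one-sided 95% bound (the lower limit of a two-sided 90% CI), the two sections would agree and 80% would be right. That is possible, but nothing in the text says so, and a reader applying the Analysis section as written would compute an ordinary two-sided 95% CI. If the one-sided bound was intended, the rule needs to say so. The text must change on either reading.

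**70% is the least favourable corner.** The article assumes resolution of at least 80% and dropout of up to 20%. With 10% dropout (222.75 per arm) power at 80% resolution is about 75%, and with 85% resolution at 198 per arm it is 79.6%. This is true and limits the practical size of the problem. It does not rescue the statement, because the article claims 80% power for that same corner: 198 evaluable per arm and a rate as low as 80%.

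**The error is on the safe side for false positives.** This also stands. The 95% CI rule is stricter than the 5% used for the sample size, so the risk of wrongly declaring non-inferiority does not rise. The cost is a greater chance of an inconclusive trial, and a wrong power figure in print.

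**The per-protocol loss is speculative.** Largely fair. The rates are assumed. The acceptance sentence names no analysis set. Loss to follow-up is already within the 20%, and later antibiotics at the physician's discretion are part of the watchful-waiting arm as defined under Intervention/Comparison, so further attrition may be small. The conclusion does not rest on these figures.

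**Conclusion.** The concern holds: the power statement is wrong as written. The sample size was evidently set at one-sided 5%, while the decision rule, on its conventional reading, works at one-sided 2.5%, and no other part of the article reconciles them. Under that rule the power is about 70%, so the chance of missing true equivalence is about 30% instead of the implied 20%. This rests on a two-sided 95% CI, 80% resolution in both arms, no true difference, a 10-point margin and 198 evaluable children per arm. All but the two-sidedness of the interval are the protocol's own premises. The validity of a positive result is not in question.

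**What to change.** Settle on one error rate and use it in the abstract, the sample-size section and the Analysis section.

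- **Preferred:** keep the 95% CI rule, call it two-sided, and restate the power along these lines: *198 evaluable children per arm give 80% power at one-sided 5% (90% CI) and about 70% power for the two-sided 95% CI on which non-inferiority is judged, if 80% resolve in both arms.*
- **If one-sided 5% was intended:** change the rule in the Analysis section to the lower limit of a two-sided 90% CI and label it as one-sided 5%. The 80% then stands.

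In either case, it would help to add the power of the per-protocol comparison under a stated non-adherence rate. Fix and date the choice before any unblinded data are seen.

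The cost is wording in the protocol and SAP. Under the preferred option the published power becomes less favourable, and no extra children are needed. Restoring 80% power under the 95% CI rule would be a different decision, with 630 recruited instead of 495.
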